## Abstract

**Introduction:**

Hyperthyroidism is a common condition affecting up to 3% of the UK population. Treatment improves symptoms and reduces the risk of atrial fibrillation and stroke that contribute to increased mortality. The most common symptom is weight loss, which is reversed during treatment. However, the weight regain may be excessive, contributing to increased risk of obesity. Current treatment options include antithyroid drugs, radioiodine and thyroidectomy. Whether there are differences in either weight change or the long-term cardiometabolic risk between the three treatments is unclear.

**Methods and analysis:**

The study will establish the natural history of weight change in hyperthyroidism, investigate the risk of obesity and risks of cardiometabolic conditions and death relative to the treatment. The data on patients diagnosed with hyperthyroidism between 1 January 1996 and 31 December 2015 will come from Clinical Practice Research Datalink linked to Hospital Episode Statistics and Office of National Statistics Death Registry. The weight changes will be modelled using a flexible joint modelling, accounting for mortality. Obesity prevalence in the general population will be sourced from Health Survey for England and compared with the post-treatment prevalence of obesity in patients with hyperthyroidism. The incidence and time-to-event of major adverse cardiovascular events, other cardiometabolic outcomes and mortality will be compared between the treatments using the inverse propensity weighting model. Incidence rate ratios of outcomes will be modelled with Poisson regression. Time to event will be analysed using Cox proportional hazards model. A competing risks approach will be adopted to estimate comparative incidences to allow for the impact of mortality.

**Ethics and dissemination:**

The study will bring new knowledge on the risk of developing obesity, cardiometabolic morbidity and mortality following treatment for hyperthyroidism to inform clinical practice and public health policies. The results will be disseminated via open-access peer-reviewed publications and directly to the patients and public groups (Independent Scientific Advisory Committee protocol approval #20_000185).

Strengths and limitations of this studyRich data from a large sample allowing for pre-exposure history and long follow-up, spanning across primary and secondary care.Contextualisation of post-treatment obesity prevalence by comparison with the general population adjusted for sex and age.A broad range of patient-relevant cardiometabolic outcomes will be evaluated.Large real-world observational study of treatment options not amenable to randomised clinical trials.The study’s main limitations are related to the intrinsic nature of the real-world data, such as the secondary use of data or the presence of missing data.

## Introduction

Hyperthyroidism is a common condition affecting 3% of women and 0.3% of men in the UK.^1^ Common clinical features indicating hyperthyroidism include weight loss, heat intolerance, tremor, palpitations and anxiety.^2^ Treatment is critical to minimise complications including atrial fibrillation and stroke that contribute to the observed 20% increase in mortality.^3^

There are three treatment options: antithyroid drugs (ATDs), radioactive iodine (I-131, radioiodine) or surgical, either as a total or hemithyroidectomy. ATDs are associated with a high rate of relapse (30%–70%),^4^ while treatment with radioiodine or thyroidectomy leads to the development of hypothyroidism, requiring lifelong levothyroxine replacement, which is seen in 80% of patients administered radioiodine and up to 100% undergoing thyroidectomy. Guidance recommends discussion of all three options with the patient.^5 6^ There is insufficient evidence to recommend one treatment over the others, although some studies indicate differences in cardiac events and mortality between the treatment modalities.^7 8^

Weight gain following various treatments for hyperthyroidism has been described.^9 10^ Clinicians commonly assume that the observed weight gain is a simple regain of weight lost prior to the initiation of treatment. However, an analysis of 1373 patients with hyperthyroidism has demonstrated a higher prevalence of obesity at 3 years of follow-up when compared with the age-matched and sex-matched background population (37% vs 26% in men, p<0.001; 32% vs 26% in women, p<0.001).^11^ These findings suggest excess weight gain beyond patients’ premorbid weight (weight overshoot). Additionally, the study showed significant differences in final weight gain compared with baseline between those treated with ATDs (5.4 kg, 95% CI 4.8 to 6.0) and those who received radioiodine but did not develop hypothyroidism (5.1 kg, 95% CI 4.3 to 6.1) when compared with those treated with radioiodine who developed subsequent hypothyroidism (7.1 kg, 95% CI 6.6 to 7.7). The extent of weight change in patients treated with thyroidectomy was not evaluated.

Prior to diagnosis, the majority of patients with hyperthyroidism notice that they lose weight, often despite increased appetite, due to the regulatory effects of thyroid hormones on metabolism. As thyroid hormone levels normalise following treatment, weight change may be observed. While weight gain following treatment is common, it may become a major psychological stressor and can affect treatment compliance. Untreated hyperthyroidism may result in serious consequences, including thyroid storm, heart failure, embolic events, atrial fibrillation, osteoporosis, muscle weakness, neuropsychiatric symptoms and, rarely, cardiovascular collapse and death.^12^ Patients need to be appropriately counselled about the possibility of significant weight gain associated with the treatment of hyperthyroidism. However, there are currently insufficient data available about weight overshoot, cardiovascular risk and treatment modality selection to provide clear guidance to our patients. In our recent survey of British Thyroid Association members, of 35 clinicians who responded, only 23% usually discuss weight gain with patients treated for hyperthyroidism despite 70% of respondents feeling this was a significant clinical problem.

We recently surveyed doctors and dieticians and found that while there was agreement that weight gain following treatment for hyperthyroidism represents a medical problem, there is no consensus about the significance of or the approach to this anticipated weight gain. When surveyed, dieticians expressed concerns that they are not equipped to advise on dietary issues, given the switch from a highly catabolic state (weight loss state) in untreated hyperthyroidism to a situation of anticipated weight gain following treatment.

As previously shown, hyperthyroidism is associated with increased cardiovascular morbidity and mortality, which are not completely reversed by treatment.^7 8 13 14^ Among cardiovascular comorbidities, atrial fibrillation is the most common, occurring in 2%–20% of untreated patients,^15^ and complications including heart failure and thromboembolic events are observed in patients with hyperthyroidism. In a recent meta-analysis, an increased risk of atrial fibrillation with higher concentrations of thyroid hormones at presentation was confirmed.^16^ In a nationwide register study with a mean follow-up time of 10 years, an increased risk of all arrhythmias was found in patients undergoing treatment with radioiodine or thyroidectomy when compared with controls with no thyroid dysfunction.^8^ Patients with subclinical hyperthyroid and hypothyroid dysfunctions were found to have increased risks of heart failure (HR=1.94, 95%CI 1.01 to 3.72 for thyroid-stimulating hormone (TSH) <0.10 mIU/L and HR=1.86, 95% CI 1.27 to 2.72 for TSH >10.0 mIU/L) in a pooled analysis of individual participant data using available prospective cohorts with thyroid function tests and subsequent follow-up of heart failure.^17^ In a large cohort of UK patients on levothyroxine replacement, mortality was increased in the lowest (<0.1) and highest TSH categories (>4.0) compared with 2.0–2.5 mIU/L, while risks of ischaemic heart disease and heart failure were found to increase at high concentrations of TSH (>10.0 mIU/L).^18^

There is insufficient evidence to systematically review the differences in health outcomes between the three different treatments. Due to limitations arising from the need to adhere to radiation protection and varied requirements of the procedures (a prolonged course of medication, one-off radioiodine tablet or surgical procedure), randomisation and blinding between all three modalities is often not possible, making randomised controlled trials nearly non-existent in this area of research.

At our recent patient engagement event, patients felt that there was insufficient information to help guide the choice of treatment. They were concerned about the risk of excessive weight gain and its long-term cardiometabolic consequences and frustrated with the lack of information, allowing them to prioritise one treatment over the other. There was also disappointment about the lack of support services addressing weight and diet across treatment for hyperthyroidism. Patients were particularly concerned about the perceived risk of weight gain associated with radioactive iodine and agreed that proper quantification of weight gain and cardiovascular risks across the treatments would influence their therapy preferences and could inform anticipatory dietary modification.

### Aims and objectives

The overall aim of this study was to investigate the risks of gaining weight and developing obesity, developing cardiometabolic conditions or death following treatment for hyperthyroidism and to compare these risks between the three treatment modalities.

#### Primary objective

The primary aim of this study was to assess the effect of type of treatment on weight changes during and after therapy for hyperthyroidism. The post-treatment prevalence of obesity will also be evaluated and compared with that of the general population.

#### Secondary objectives

Further, the effect of treatment and weight status on the incidence of major adverse cardiovascular events (MACEs), other cardiometabolic outcomes and mortality following each treatment modality will be evaluated.

## Methods

This is a retrospective, longitudinal, observational study using routinely collected data. Data for the study will come from the Clinical Practice Research Datalink (CPRD), linked to Hospital Episode Statistics (HES) admissions and outpatient databases. The study is to be conducted between 1 February 2021 and 31 July 2022. The protocol was approved by the Independent Scientific Advisory Committee (ISAC #20_000185).

### Data sources

CPRD collects and anonymises patient electronic health record data from a network of general practitioner (GP) practices across the UK.^19^ Although the records in the database cover all four UK countries, HES-linkable records are limited to those from England only. Two HES datasets will be used: HES outpatient and HES admitted patient care. Linkage to HES databases is required to obtain the data, which may be missing from the GP records on non-medical treatment for hyperthyroidism (radioactive iodine and thyroidectomy). Additionally, data on MACEs will also be sourced from HES, as such events are typically being treated in the hospital setting.

Linkage to social data is required to adjust the analysis for socioeconomic status, which is a known risk factor for obesity and increased mortality. This will be obtained as the Index of Multiple Deprivation (IMD). Linkage to Office of National Statistics data is required to get access to the date of death and cause of death. Prevalence of post-treatment obesity will be compared with the background population sourced from Health Survey for England, a yearly survey monitoring trends in the nation’s health and care.

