### Population

Adult patients (≥18 years) who were for the first time diagnosed with hyperthyroidism (the list of codes in online supplemental appendix) between 1 January 1996 and 31 December 2015 will be eligible for inclusion. To minimise missed cases, the diagnosis will be additionally identified by a prescription of carbimazole or propylthiouracil, which are ATDs indicated only for treatment of hyperthyroidism. A minimum of 12 months of data must be available before the date of diagnosis and after the index date. CPRD records need to be classified as acceptable research quality.

10.1136/bmjopen-2021-055219.supp1Supplementary data

Exclusion criteria encompass ATD treatment of duration shorter than 6 months as the only treatment, that is, with no radioactive iodine or thyroidectomy followed. This is to avoid contamination by misdiagnosis or spontaneously resolving thyroiditis. Patients treated with both definitive treatment methods, that is, radioiodine and thyroidectomy, will also be excluded. However, ATD treatment followed by either radioiodine or thyroidectomy (one of the definitive treatments) is considered a pretreatment and does not constitute an exclusion criterion.

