### Exposure

The exposure in the study is the treatment for hyperthyroidism. The study patients will be divided into three groups based on the treatment administered: (1) radioiodine: the allocation to this treatment arm will be assigned based on the Read code or OPCS-4 code of the treatment procedure for radioiodine; (2) thyroidectomy: the allocation to this treatment arm will be assigned based on the Read code or OPCS-4 code of the surgical procedure; (3) medical treatment arm will be identified based on the absence of radioiodine treatment code and thyroidectomy code in the presence of ATD treatment (based on the Read code or British National Formulary (BNF) code) longer than 6 months.

We anticipate good quality of ATD prescription and thyroidectomy. However, radioiodine, typically administered in outpatients, may be missed in a substantially high proportion of patients. Since ATD treatment does not incur permanent hypothyroidism, the long-term prescription of levothyroxine for hypothyroidism following treatment with ATD alone, that is, without any definitive procedures, will be considered as a proxy for radioiodine administration.

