### Outcomes

The primary outcome is weight change (in kilogram) during and following the treatment for hyperthyroidism, as well as prevalence of obesity following the treatment. The secondary outcomes include cardiometabolic events and mortality as presented in table 1.

**Table 1 T1:** Secondary outcomes and their data sources

Secondary outcome	Source
MACE (cardiovascular death, nonfatal myocardial infarction or non-fatal stroke)	HES
Type 2 diabetes mellitus	CPRD
Congestive heart failure	HES
Ischaemic heart disease	HES
Stroke and transient ischaemic attack	HES
Cardiovascular mortality	ONS
All-cause mortality	ONS

CPRD, Clinical Practice Research Database; HES, Health Episode Statistics; MACE, major adverse cardiovascular event; ONS, Office for National Statistics.

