### Index date and follow-up

The index date in the cohort is the date of initiation of treatment for hyperthyroidism, which defines the treatment group (either ATD, radioiodine or thyroidectomy). There is a requirement of at least 12 months’ data available prior to the index date.

The natural history of weight changes will be modelled preindex and postindex date. While the follow-up for the analysis of outcomes will start at the index date, a minimum of 12-month follow-up is required for the inclusion.

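### Heart failure, ischaemic heart disease and stroke/TIA are taken from HES only, with no stated removal of existing disease, so disease already known to the GP can be counted as incident, possibly more readily after thyroidectomy

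*Protocol article*

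**What the plan says.** Table 1 (Methods, Outcomes) assigns one data source to each secondary outcome. The three rows at issue read "Congestive heart failure HES", "Ischaemic heart disease HES" and "Stroke and transient ischaemic attack HES". Type 2 diabetes is assigned to CPRD, and the two mortality outcomes to ONS.

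The reason for using HES is in Data sources: "Additionally, data on MACEs will also be sourced from HES, as such events are typically being treated in the hospital setting". Table 1 defines MACE as cardiovascular death, non-fatal myocardial infarction or non-fatal stroke. The same section says that HES outpatient as well as admitted-patient data will be used.

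Population states two treatment-based exclusions. One begins "Exclusion criteria encompass ATD treatment of duration shorter than 6 months as the only treatment"; the other removes patients who had both definitive treatments. Neither concerns prior cardiovascular disease.

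Index date and follow-up sets the index date at the start of the treatment that defines the group. It requires 12 months of earlier data and continues: "While the follow-up for the analysis of outcomes will start at the index date". For surgical patients, Exposure says that "the allocation to this treatment arm will be assigned based on the Read code or OPCS-4 code of the surgical procedure".

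Confounding names comorbidities among the baseline adjusters, but Table 2 does not define them. The propensity covariate list under Cardiometabolic risks and mortality contains neither comorbidities nor prior cardiovascular disease.

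**The concern.** The secondary objective is the incidence of these outcomes after each treatment, analysed as rates and as time to first event. Such an analysis needs an at-risk set free of the condition at time zero and a source that sees the condition when it first appears. For these three outcomes the article fixes neither.

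Heart failure, stable ischaemic heart disease and TIA can be diagnosed and managed in general practice. A patient whose angina has been in the GP record for years, but never in HES, has no HES event before the index date. The first later hospital contact that codes it would look like a new case. Conversely, a new diagnosis managed only by the GP would never be counted.

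The first of these errors may also differ by arm. Thyroidectomy brings a hospital procedure at time zero. Starting ATD implies no admission, and the article says radioiodine is usually given to outpatients. If diagnoses coded at the surgical stay count as outcomes, old disease appears as a cluster of day-0 events in one arm only. That would bias the treatment comparison and could also disturb the proportional-hazards check that decides which time-to-event model is used.

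**Working it through.** **Text check.** The article gives no event rates, sample size or power figure for these outcomes, so there is no stated figure to reproduce.

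1. Source: HES is the only one listed for the three outcomes. CPRD is listed for type 2 diabetes, so sources were chosen outcome by outcome.
2. Reason: it is given for MACE, whose non-fatal components are acute. Heart failure, chronic ischaemic heart disease and TIA are not MACE components.
3. At-risk set: no stated exclusion removes prior disease. The 12-month look-back is an eligibility rule and is not linked to finding existing disease.
4. Time zero: the index date, with no lag stated.
5. Not stated: whether HES diagnoses count in any position or only as primary, how an event is dated within a stay, and how codes from the index admission are treated.

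**Illustration of size. Every input is assumed, and there is no true treatment effect.**

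- *q*: share of patients with long-standing disease known to the GP but never coded in HES, 1% to 5%, equal in both arms.
- *c*: probability that this disease is coded at the index stay, 0.8 for thyroidectomy and 0 for ATD.
- *a*: yearly rate at which it is first coded at a later hospital contact, 0.10 in both arms.
- *h*: true incidence, 5 to 20 per 1000 person-years.
- *T*: years of follow-up. Deaths are ignored.

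Apparent rate = events / person-years, where

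- disease-free patients: events = (1−q)(1−e^(−hT)); person-years = events / h
- prevalent patients, with l = a + h: events = q[c + (1−c)(1−e^(−lT))]; person-years = q(1−c)(1−e^(−lT)) / l

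Worked case: h = 0.01, q = 0.03, T = 5.

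- Disease-free, both arms: events 0.97 × 0.04877 = 0.0473; person-years 4.731.
- 1−e^(−0.11×5) = 0.4231.
- Surgery, prevalent: events 0.03 × (0.8 + 0.2 × 0.4231) = 0.0265; person-years 0.03 × 0.2 × 0.4231 / 0.11 = 0.0231. Rate = 0.0738 / 4.754 = 15.5 per 1000.
- ATD, prevalent: events 0.03 × 0.4231 = 0.0127; person-years 0.0127 / 0.11 = 0.1154. Rate = 0.0600 / 4.846 = 12.4 per 1000.
- Ratio = 15.5 / 12.4 = 1.25, where the truth is 10 per 1000 in both arms and a ratio of 1.00.

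Full grid (rates per 1000 person-years):

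| True rate | q | ATD, 5 y | Surgery, 5 y | Ratio, 5 y | ATD, 10 y | Surgery, 10 y | Ratio, 10 y |
|---|---|---|---|---|---|---|---|
| 5 | 1% | 5.8 | 6.8 | 1.17 | 5.6 | 6.0 | 1.06 |
| 5 | 3% | 7.4 | 10.5 | 1.42 | 6.9 | 7.9 | 1.14 |
| 5 | 5% | 9.0 | 14.3 | 1.59 | 8.2 | 10.0 | 1.21 |
| 10 | 1% | 10.8 | 11.8 | 1.09 | 10.6 | 11.0 | 1.03 |
| 10 | 3% | 12.4 | 15.5 | 1.25 | 11.9 | 13.0 | 1.09 |
| 10 | 5% | 14.0 | 19.4 | 1.39 | 13.2 | 15.1 | 1.14 |
| 20 | 1% | 20.8 | 21.9 | 1.05 | 20.6 | 21.0 | 1.02 |
| 20 | 3% | 22.4 | 25.7 | 1.15 | 21.9 | 23.1 | 1.05 |
| 20 | 5% | 24.0 | 29.6 | 1.23 | 23.3 | 25.3 | 1.09 |

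Over 1 year the ratio runs from 1.35 to 4.89, because the day-0 codes are set against little person-time.

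Two checks. With q = 0 (prior disease removed) the ratio is 1.00 in every cell. If index-stay codes are not counted (c = 0 for surgery too), the surgical rate falls to the ATD rate and the ratio is again 1.00. Both rates still exceed the truth: in the worked case by 12.4 / 10 = 1.24. The model does not cover GP-managed new events that HES misses.

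**The case against.** The strongest reply is that a journal article condenses a longer approved protocol, with code lists in a supplement. Code position, event dating, index-stay handling and washout could be set there. This stands as far as the thyroidectomy stay is concerned. A reader might infer that old disease coded at the index thyroidectomy admission will be scored as an incident event. The article does not say so, and a primary-position or index-stay rule would remove that component.

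Other points in the plan's favour:

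- HES outpatient data are also used, so a hospital admission is not the only route into HES.
- The source column may not be exhaustive. The MACE row lists HES only, although it includes cardiovascular death and ONS supplies cause of death. But nothing in the article adds CPRD as a source for the three outcomes.
- Baseline comorbidities are among the adjusters. Being undefined, they may or may not include prior cardiovascular disease. Even if they do, adjustment does not turn a first hospital coding of old disease into a new event.
- Hospital-only outcomes trade sensitivity for specificity, which is a legitimate choice. It is a better choice for a sensitivity analysis than for the sole definition of conditions often recorded first in general practice.

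A reader might also infer a doubling of risk. A cruder sum gives (5% + 0.5 × 10%) / 5% = 2.0 over 10 years. It requires that 10% of patients have such uncoded disease, that half of the surgical cases are coded on day 0, and that no ATD case is coded in HES in a decade. Nothing in the article supports those inputs.

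**Conclusion.** The point holds in conditional form. As stated, the plan can count GP-known heart failure, ischaemic heart disease and stroke/TIA as incident, and it misses new cases managed only by the GP. That rests on the text: the single listed source, a reason that covers MACE only, no stated handling of prior disease, and follow-up from the index date.

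That the error is greater for thyroidectomy is plausible but not established, since it depends on coding rules the article does not give. If those rules do not prevent it, the illustration puts the spurious surgery-versus-ATD rate ratio at about 1.05 to 1.59 over 5 years and 1.02 to 1.21 over 10 years, diluting as follow-up lengthens. These figures show direction and order of size only; the true size is unknown.

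The outcomes affected are secondary, but they carry the comparison of cardiometabolic risk between treatments, so the change should be made.

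**What to change.** For congestive heart failure, ischaemic heart disease and stroke/TIA:

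1. Define the event as the first-ever record in CPRD or HES, or in ONS for fatal events.
2. For each outcome separately, remove from the at-risk set any patient with that condition in any source before the index date.
3. State how codes from the index admission are treated. Do not count codes for pre-existing chronic disease, but keep genuine acute perioperative events. A rule that accepts only primary diagnoses at that stay is too blunt: the main diagnosis may be the thyroid disease, and dropping a real perioperative infarction or stroke would favour surgery.
4. Keep the HES-only definition as a sensitivity analysis.

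The sources are already part of the planned linkage, so the cost is code lists and wording. The downside is fewer at-risk patients per outcome and somewhat lower specificity for GP-coded events.
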